### Intervention

The treatment group will receive a 6-day course of commercially available vaginal clotrimazole pessaries (Canestan^®^). Women will be advised to insert one pessary as gently and deeply as possible into the vagina while lying on her back, preferably at night, for 6 nights. We have chosen 6 days of treatment because this is: supported by the Cochrane Systematic Review of treatment for *Candida *eradication in pregnancy [36], this is how commercially available vaginal clotrimazole is marketed[40] and this was the regimen used in the Kiss trial [14]. Women who miss one or more daily doses will be advised to insert a single pessary as soon as they remember or the next evening, and continue using the pessaries until the course of treatment is finished.

### Follow-up

A brief (< 5 minutes) follow-up questionnaire will collect information about symptoms of candidiasis, use of antibiotics and/or corticosteroids (risk factors for symptomatic candidiasis), treatment of candidiasis (including study medication, doctor prescribed and over-the-counter medications), treatment side-effects and compliance with the treatment regimen. The questionnaire will be web-based with email notification or mailed with a reply-paid envelope according to the participants stated preference at trial entry. These secondary outcomes will be collected at 28-32 weeks, a gestation when the potential for unmasking the 'no treatment' arm will be irrelevant.

Care of all women and their babies will be otherwise managed according to the standard practices of the model of maternity care she has chosen. Women who develop symptoms of *Candida *infection will be offered appropriate treatment. The results of the vaginal swab culture taken at the time of trial entry will not be disclosed nor be available in the pregnancy record.

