### Recruitment and collection of baseline data

The study procedure is feasible as it draws on usual antenatal care in pregnancy, and is similar to the Kiss trial (see Table 1). The research nurse will ask eligible women to participate, explain the trial and obtain informed consent, collect baseline data and ask women to self-collect a vaginal swab. This is only a minor departure from current practice.

**Table 1 T1:** Trial Schema

		Timing (data collection)
Identification & screening of eligible women (N = 16,040)*		Routine antenatal visit at 12-19 weeks (baseline data, *Candida *testing)
**↓**		
Randomisation of women with asymptomatic *Candida *(n = 3208)		< 1 week after *Candida *testing
**Clotrimazole** **↓**	**Usual care** **↓**	
Follow-up	Follow-up	28-32 weeks gestation (questionnaire)
**↓**	**↓**	
Birth	Birth	Primary and secondary outcomes collected from obstetric database

* primary outcome data (preterm birth rates) will be obtained for all women screened regardless of the result

As women of child-bearing age are known to be very mobile [47], participants will be asked to provide their parents and other alternative contact details (eg friend or relative) to enhance subsequent follow-up. Women will also be asked to specify their preferred method of contact - women in our pilot study have shown a strong preference for email contact. Self-collection of vaginal swabs is commonly used for screening in pregnancy [48]. We have also successfully used this method of specimen collection in a study of vaginal *Ureaplasma urealyticum *colonisation in pregnancy[49] and in our pilot study [43]. The detection rate of *Candida *using self-collection is not different from techniques that are more invasive, requiring the use of a speculum [50].

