### Randomisation

Eligible women who are culture positive for *Candida *will be randomised to receive active treatment with clotrimazole or usual care. The randomisation schedule will be prepared and centrally administered by a researcher not involved in patient care. A computer random number generator will be used to prepare the randomisation schedule with permuted blocks and 1:1 randomisation. The women randomised to open-label clotrimazole treatment will be notified by phone by a research nurse. A central pharmacy will be responsible for dispensing the study medication which will be sent to participants by mail from the coordinating centre. This approach has been acceptable and successful in the pilot study.

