### Isolation and identification of *Candida *from vaginal swabs

The detection and identification of *Candida *from vaginal swabs is readily achieved. The swab will be inoculated onto full-plates of chromogenic agar (CHROMagar™Candida, CHROMagar, Paris, France) to isolate, provisionally speciate and semi-quantitatively enumerate (scant, moderate, or heavy) *Candida *species and to obtain colonies for further work such as susceptibility testing by broth microdilution methods. This medium is chosen to ensure detection of mixed infections. Cultures will be incubated for 72 hours at 35°C in 5% CO_2_. Identification to species level will be based on colony morphology, and colour.

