### Interim analyses: the Data Monitoring Committee

An independent Data Monitoring Committee (DMC) with established terms of reference and stopping rules will be appointed to review interim data and other evidence (including updated overviews of relevant randomised controlled trials). The DMC will:

• Advise on protocol modifications suggested by investigators or collaborators (e.g. sample size or trial endpoint modifications)

• Assess the impact and relevance of new external evidence

• Assess data quality, including completeness

• Monitor recruitment figures, balance in recruitment by centre and losses to follow-up

• Monitor evidence for treatment harm

• Monitor planned sample size assumptions

• Monitor treatment side-effects and compliance with the treatment regimen

• Recommend that the trial continues to recruit participants or that recruitment should be terminated

An interim analysis will be conducted when outcomes are known for the first 50% of women recruited. The O'Brien-Fleming method[58] will be used to preserve the overall P-value at 0.05; for the interim analysis we will test at P = 0.0031 (z = 2.95430) and for the final analysis at P = 0.0497 (z = 1.96257) (these calculations were performed using PASS).

The DMC will inform the Steering Group if in their view an arm of the study is either clearly indicated or contra-indicated. The final decision on whether to stop the trial will rest with the Steering Group.

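### As the article describes it, side-effects and compliance for the 6-night course are collected about 5 to 19 weeks after it ends, for an unmasking reason that does not apply to these items in the open-label treated arm

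*Protocol article*

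**What the plan says.** The Follow-up section of the protocol article describes one brief questionnaire, by web or post. It covers candidiasis symptoms, antibiotic and corticosteroid use, any treatment of candidiasis (study, prescribed or over-the-counter), and "treatment side-effects and compliance with the treatment regimen". On timing it says: "These secondary outcomes will be collected at 28-32 weeks, a gestation when the potential for unmasking the 'no treatment' arm will be irrelevant". No other reason is given. The trial schema (Table 1) shows the same single follow-up contact between randomisation and birth.

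Under Randomisation, women allocated to clotrimazole are told so by a research nurse by telephone, and the medication is "sent to participants by mail from the coordinating centre". Usual-care women do not learn their swab result.

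The DMC's listed duties include: "Monitor treatment side-effects and compliance with the treatment regimen". The article names no separate data source for that duty.

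**The concern.** Side-effects of the allocated pessaries, and compliance with them, exist only in the clotrimazole arm. Those women already know their allocation, so the unmasking argument gives no ground for waiting until 28-32 weeks to ask them. Two things follow from the delay.

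- **Recall.** The local reactions named in the background (burning, stinging, redness) would be expected around the nights of use, and the number of nights used is a detailed item. Both are asked about weeks to months later. The protocol's own evidence shows that course length matters: it cites 98% eradication with 7 days against 49% with 4 days. The article describes no post-treatment swab. Reported use is therefore the described means of telling an ineffective treatment from a mailed course that was not completed.
- **Missingness tied to outcome.** Pregnancies that end before 28 weeks never reach the questionnaire as scheduled. These include losses before 20 weeks (a listed secondary outcome) and the earliest preterm births. Adherence and tolerability would be unknown for women whose outcomes matter most to the trial.

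**Working it through.** The article states no recall interval, so there is no plan figure to reproduce. The interval is built from the stated timings.

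**Inputs**

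- Swab: "Routine antenatal visit at 12-19 weeks" (Table 1), read as 12+0 to 19+6 weeks.
- Transport to the laboratory: within 24 hours (Specimen collection and transport).
- Culture: "Cultures will be incubated for 72 hours at 35°C" (Isolation and identification). Transport plus culture gives about 1 + 3 = 4 days as the short case from swab to randomisation.
- Swab to randomisation: under 1 week (Table 1), so 7 days as the upper bound.
- Mailing: by post, duration not stated. **Assumed 2 to 7 days.**
- Course: 6 nights (Intervention).
- Questionnaire: 28-32 weeks, read as 28+0 to 32+6.

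**Formulas**

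End of course = swab + time to randomisation + mailing + 6 days. Recall gap = questionnaire − end of course.

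| Case | End of course | Questionnaire | Gap |
|---|---|---|---|
| Longest | 12+0 + 4 + 2 + 6 days = 84 + 12 = 96 days (13+5) | 32+6 = 230 days | 230 − 96 = 134 days = 19.1 weeks |
| Shortest | 19+6 + 7 + 7 + 6 days = 139 + 20 = 159 days (22+5) | 28+0 = 196 days | 196 − 159 = 37 days = 5.3 weeks |

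**Sensitivity**

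- Mailing time set to zero in the shortest case: 196 − (139 + 7 + 0 + 6) = 44 days, or 6.3 weeks.
- Upper end of the questionnaire window read as 32+0 (224 days) in the longest case: 224 − 96 = 128 days, or 18.3 weeks.

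The range of about 5 to 19 weeks therefore depends little on the one assumed input or on how the week limits are read.

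**Does the stated reason cover these items?**

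| Item on the questionnaire | Arm it concerns | Would early collection unmask a usual-care woman? |
|---|---|---|
| Symptoms, antibiotics, corticosteroids, other antifungal use | Both | It could; a common late time point is reasonable |
| Compliance with the allocated course | Clotrimazole only | No; a form in the clotrimazole pack never reaches her |
| Reactions to the allocated course | Clotrimazole only | No, for the same reason |

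The planned size of the treated arm is 1,604, so the timing applies to all treated women who reach the questionnaire.

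**The case against.** The strongest case on the other side has five parts.

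1. **The article is condensed.** The full protocol may hold an adverse-event route, a reaction contact line or a check during the nurse's call. A reader might infer that the questionnaire is the trial's sole tolerability and adherence measure. The article does not establish that; it only names no other. This stands, and the point is limited to what the article describes.
2. **Recall error is not demonstrated.** The documents give the length of the interval but nothing on misclassification. Whether a six-pessary pack was used at all may well be remembered. This stands: the calculation measures delay, not error.
3. **One instrument in both arms has value.** Usual-care women may be treated if symptoms develop, or may buy clotrimazole over the counter, so treatment reactions can occur there too. Symptoms of candidiasis also overlap with reactions to the drug. Replacing the common questionnaire with a treated-arm record would make ascertainment differ by arm. This stands against replacement, but not against adding a form.
4. **A nightly diary could prompt use** and move the trial away from the routine practice that the PROBE design is meant to reflect. This also stands, and it argues for a single form after the course.
5. **The DMC is barely affected at its scheduled look.** A reader might infer that it would lack these data at the interim analysis. That analysis waits for birth outcomes in the first 50% of women. By then those women will have given birth or passed the questionnaire window, so returned questionnaires will be available. Only monitoring before or between formal looks is delayed.

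None of this supplies a reason for the late timing of these two items in the treated arm, and none answers the loss of women whose pregnancies end before 28 weeks.

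**Conclusion.** The point holds as a weakness in secondary data. In the article as written, compliance with and reactions to the 6-night course are collected about 5 to 19 weeks after it ends, and the reason given does not apply to those items in the open-label arm. The data would also be missing for women whose pregnancy ends before 28 weeks, and hence in relation to outcome.

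The interval rests on the stated timings plus an assumed 2 to 7 days for mailing. The degree of recall error is unknown.

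A reader might go further and infer bias in the main result. The documents do not support that: the primary outcome comes from obstetric and hospital databases, is assessed blind and is compared by intention to treat, and the Analyses section plans no compliance-based analysis of it. What is weakened is the tolerability statement, the explanation of a null result, and DMC monitoring between looks. It is worth changing because the change is cheap.

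**What to change.** Add one short end-of-course form to the clotrimazole pack, asking for the number of pessaries used and any local reaction. Have it returned reply-paid or through the web link already planned for follow-up. Name it as the source for compliance and treatment reactions, including what the DMC receives between looks. Use a single form completed after the last night rather than a nightly record, so that the form does not itself prompt adherence.

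Keep the full 28-32 week questionnaire unchanged in both arms. Symptoms, other antifungal use and any between-arm comparison of complaints then still rest on the same instrument at the same time. State in the Follow-up section that the unmasking reason applies to these common items.

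The cost is one page and a return envelope or link in a pack already being posted, with no extra visit. The downside is one extra form, with some non-return, in the treated arm only. If the full protocol already has an earlier source for these items, citing it in the Follow-up and DMC sections would be enough.

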### Outcomes and Explanatory Factors

#### Baseline data

Brief baseline data will be collected to assess comparability of the study groups. The baseline assessment will include age, socio-demographic data, smoking and alcohol use, medical conditions, history of candidiasis, history of prior pregnancies including preterm birth, gestational age at enrolment and method of gestational age assessment (ultrasound or dates). This information will be obtained from existing databases (as outlined below) or where this is not available from the participants at study entry.

##### Primary Outcome

birth <37 weeks gestation following spontaneous onset of labour or following preterm prelabour rupture of membranes.

The primary and secondary outcomes will be obtained (with informed consent) from existing computerised obstetric and hospital databases. This is a novel and cost-efficient approach [51]. We have previously demonstrated that the outcomes for this study are reliably collected in routinely collected obstetric and hospital databases [52-56]. It also allows identification of transfers to another hospital. The latter are uncommon and we will utilise health record linkage to determine outcomes for these few women who would otherwise be lost to follow-up. Consequently, we anticipate negligible loss to follow-up in this trial. Because this approach is novel, we will validate the primary outcome (preterm birth) by reviewing the medical records of all women identified in the computerised databases as delivering preterm, those where gestational age is missing (usually <1%) and a random sample of those recorded as term deliveries. We estimate that approximately 300 records will need to be reviewed to validate preterm birth.

##### Secondary outcomes

Include any preterm birth <37 weeks, medically indicated preterm birth <37 weeks (including indication), preterm birth <32 weeks, preterm prelabour rupture of the membranes, spontaneous pregnancy loss <20 weeks gestation, fetal growth restriction (< 10^th ^birthweight for gestational age percentile), perinatal mortality (stillbirth or neonatal death), admission to neonatal intensive care unit, duration of stay in hospital (maternal and infant), birth weight, Apgar score at 5 minutes, and a composite neonatal morbidity indicator including respiratory distress, assisted ventilation, intraventricular haemorrhage, necrotising enterocolitis, retinopathy and pneumonia [57].

### Other maternal and infant explanatory factors

Other conditions may arise in pregnancy that influence preterm birth risk including pregnancy hypertension, gestational diabetes, antepartum haemorrhage, placental abnormalities (placenta praevia, placental abruption), congenital anomalies, onset of labour (spontaneous, induced or no labour) and mode of delivery.

### Analyses

Analyses will be by intention to treat. The primary analysis will compare the proportions of spontaneous preterm births in the two groups, using a chi-squared test. The relative risk and 95% confidence interval of preterm birth and other outcomes in women with active treatment compared with those with usual care will be calculated. In the secondary analysis of the primary outcome, logistic regression will be used to adjust for centre and any differences in important baseline characteristics. Secondary outcomes that are binary will be analysed in a similar manner, while those that are quantitative will be compared between groups using t-tests or the distribution-free equivalent, as appropriate.

Sub-group analyses will be used to explore associations between preterm birth and clotrimazole treatment by degree of *Candida *colonisation (light, moderate, heavy), *Candida albicans *and *non-albicans *species, gestational age at enrolment, and among medically indicated preterm births by indication (hypertension, growth restriction, fetal malformation, placental abnormalities). To test for differences in the effect of clotrimazole among sub-groups, a chi-squared test for interaction will be used, using the trend version for the ordered variable, degree of colonisation.

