### Sample size

A sample size of 3,208 women with *Candida *colonisation (1,604 per arm of the trial) is required to detect a 40% reduction in spontaneous preterm births (compared with term birth) among women with asymptomatic candidiasis from 5.0% in the control group to 3.0% for those women treated with clotrimazole (significance 0.05, power 0.8). This is a more conservative risk reduction than that found in the trial by Kiss [14], where analysis of this subgroup suggested treatment of asymptomatic candidiasis was associated with a 65% reduction in spontaneous preterm birth but the numbers were small and the subgroup analysis was post-hoc.

Recruitment of 3,208 women will require 16,040 women to be screened based on a *Candida *carriage rate of 20%. In our pilot study the *Candida *carriage rate was 19.6% and the participation rate among eligible women was 64%. If a participation rate of 64% could be maintained across all participating centres, ~25,000 would need to be approached to achieve screening of 16,040 women. A lower participation rate means more women would need to be approached. We expect that a participation rate of at least 60% could be maintained across all centres and this would mean approaching ~26,000 women.

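### Secondary adjusted analysis of the primary outcome: apart from centre, covariates enter only if the arms are seen to differ, so the model cannot be fixed in advance and balanced predictors are left out

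*Protocol article*

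**What the plan says.** The relevant text is in two sections of the protocol article.

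- **Analyses, primary:** "The primary analysis will compare the proportions of spontaneous preterm births in the two groups, using a chi-squared test". A relative risk with 95% confidence interval accompanies it. No covariates are involved.
- **Analyses, secondary analysis of the primary outcome:** "logistic regression will be used to adjust for centre and any differences in important baseline characteristics". Binary secondary outcomes are then to be handled in the same way.
- **Baseline data:** "Brief baseline data will be collected to assess comparability of the study groups". The items are age, socio-demographic data, smoking and alcohol, medical conditions, past candidiasis, "history of prior pregnancies including preterm birth", gestational age at enrolment and how gestational age was assessed.

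The article does not say which characteristics count as important or how large a gap counts as a difference. Those details may sit in an analysis plan that is not shown, and their absence is not the point here. The point is the rule that the article does state.

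**The concern.** Adjustment is useful when a covariate predicts the outcome. Whether the covariate happens to be unevenly spread between randomised arms is a separate matter, and in this trial (computer-generated, centrally administered 1:1 schedule) any uneven spread is chance. A rule that waits for an observed difference has two consequences.

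1. **The model cannot be fixed in advance.** Someone must first compare the arms at baseline and then decide what to adjust for. Two competent analysts could reach different models from the same data.
2. **Important predictors drop out when balanced.** History of preterm birth is collected, but under this sentence it enters only in the minority of trials where it looks unbalanced.

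At stake is the standing of the adjusted result for the primary outcome, and possibly of the adjusted results for the binary secondary outcomes. The trial's main test is not at stake.

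**Working it through.** **Step 1. Does the sample size depend on the adjusted model?**
Inputs (Sample size section): 5.0% versus 3.0%, significance 0.05, power 0.8, 1,604 per arm. Two-sided testing is inferred from the final-analysis boundary in the interim analyses section: z = 1.96257 gives two-sided P = 0.0497.

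Uncorrected: n = [z(0.975)·√(2·0.04·0.96) + z(0.80)·√(0.05·0.95 + 0.03·0.97)]² / 0.02² = (0.5432 + 0.2329)² / 0.0004 = 1,505.8, so 1,506.

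Continuity-corrected: (n/4)·[1 + √(1 + 4/(0.02·n))]² = 1,604.2 with n = 1,505.8. This matches the stated 1,604 (rounding up at each stage gives 1,605).

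The figure is reproduced by an unadjusted comparison of two proportions, so the covariate rule does not affect it.

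**Step 2. How often would chance imbalance change the model?**
The protocol gives no threshold. *Assume* that a difference means P < 0.05 and that the items are independent. The chance that at least one of k items is flagged is 1 − 0.95^k:

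| k | At least one flagged |
|---|---|
| 8 | 1 − 0.663 = 34% |
| 9 | 1 − 0.630 = 37% |
| 10 | 1 − 0.599 = 40% |

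The Baseline data section lists 8 or 9 items, depending on whether smoking and alcohol are counted together. These percentages say how often the model changes. They do not measure bias or error.

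**Step 3. How often would a strong predictor be left out?**
Simulation A had 1,604 per arm and eight binary covariates. The first had assumed prevalence 8% and odds ratio 4. With the same P < 0.05 trigger, that covariate was selected in 5.7% of 3,000 null trials and 4.8% of 2,000 trials with an effect. The rule therefore omits it in about 94–95% of trials.

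**Step 4. What does that cost?**
Simulation A used the covariates above. Simulation B assumed prior preterm birth 6% (RR 4), smoking 12% (RR 1.6), nulliparity 42% (RR 1.3) and older age 20% (RR 1.3), with 3,000 runs.

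| | Unadjusted | Selected on imbalance | Prespecified |
|---|---|---|---|
| Power, A | 0.807 | 0.811 | 0.816 |
| Power, B | 0.826 | 0.825 | 0.832 |
| Type I error, A | 0.044 | 0.043 | 0.047 |
| Type I error, B | 0.047 | 0.045 | 0.048 |

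Monte Carlo error for power in A is √(0.81·0.19/2,000) = 0.009, so its three power figures are practically equal. Reporting whichever of the three models in A was most favourable gave a type I error of 0.054. With weaker assumed effects (leading odds ratio 2) that figure was 0.048.

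In A the mean log odds ratio and its standard deviation were −0.520 and 0.181 unadjusted, against −0.534 and 0.185 prespecified. The ratios are 2.87 and 2.89. Adjustment did not narrow the spread of the logistic estimate, and any gain in power is slight.

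**Limits.** All prevalences and effects are assumptions. Centre was not modelled in A, and neither simulation tested the exact covariate list proposed below.

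**The case against.** The strongest reply is that this is a secondary analysis, labelled as such, beside a fully specified primary test. That stands, and it limits the weight of the point.

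A second reply is that the rule is not indiscriminate, because the characteristic must be important as well as different. That also stands. It would be wrong to say that the rule ignores prognosis altogether. The defect is that importance alone is not enough for a covariate to enter.

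A third reply is that the list and the threshold belong in an analysis plan. For those details it succeeds. It does not rescue the trigger: a plan that only defined the terms would keep selection on imbalance, and a plan with a fixed list would depart from this sentence.

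A reader might infer more than the documents support:

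- **That the trial's main conclusion rests on a model chosen after the fact.** It does not, because the chi-squared test is prespecified.
- **That covariates would be chosen for their effect on the result.** The rule uses baseline data by arm and makes no reference to outcomes.
- **That open-label treatment makes the choice of covariates biased.** The documents show no route for this. The listed characteristics largely predate randomisation.
- **That the strongest known predictors are being discarded.** The article does not rank predictors. It only shows that prior preterm birth and others are collected and can be omitted.
- **That the odds ratio is a problem here.** At 5% versus 3% the odds ratio is (0.03/0.97)/(0.05/0.95) = 0.59 and the relative risk is 0.60, so reporting an adjusted relative risk is a minor preference.

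**Conclusion.** The point holds as a weakness in a stated method, confined to the secondary adjusted analysis of the primary outcome and possibly extending to the binary secondary outcomes. Observed imbalance is the wrong criterion for entry, it prevents the model from being fixed beforehand, and it drops important collected predictors when they are balanced.

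Its numerical consequence is very small under the assumptions tried, as the power and type I error table shows. The figures for how often the model changes (34–40%) and how often a strong predictor is omitted (94–95%) depend on an assumed P < 0.05 trigger that the protocol does not contain. The case for change therefore rests on reproducibility and on removing discretion. Gains in power or error control are not the reason to act.

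**What to change.** In the Analyses section, keep centre and replace the clause about baseline differences with a short list prespecified for prognostic value and included whatever the observed balance. An example is centre, prior preterm birth (with nulliparous women as their own category), smoking, maternal age and gestational age at enrolment. State that the same list applies to the adjusted analyses of binary secondary outcomes, or name a different one. Keep the unadjusted chi-squared test as primary.

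The cost is about one sentence. Every covariate in the example comes from data the protocol already collects or from the recruiting centre, and the sample size does not change.

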### Setting

The study will be carried out in at least five participating maternity hospitals. A range of antenatal care options are provided in these hospitals including standard antenatal clinic care, midwifery-led care, birth centre care, GP-shared care and private obstetric care.

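### Quantitative secondary outcomes are given only unadjusted two-group tests, which is valid but gives up modest precision, most clearly for birth weight, although prognostic entry variables are already collected

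*Protocol article*

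**What the plan says.** The Analyses section of the protocol article sets a chi-squared test and a relative risk with 95% confidence interval for the primary outcome. It adds a secondary analysis in which "logistic regression will be used to adjust for centre and any differences in important baseline characteristics". It continues: "Secondary outcomes that are binary will be analysed in a similar manner". The same sentence then turns to the remaining outcomes, and "those that are quantitative will be compared between groups using t-tests or the distribution-free equivalent, as appropriate". No adjusted analysis is named for them.

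The outcomes concerned are listed under Secondary outcomes: "duration of stay in hospital (maternal and infant), birth weight, Apgar score at 5 minutes". The Apgar score belongs here only if it is analysed as a score.

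The Baseline data section lists what is recorded at entry: "age, socio-demographic data, smoking and alcohol use, medical conditions, history of candidiasis, history of prior pregnancies including preterm birth", together with gestational age at enrolment and how it was assessed. The stated purpose is comparability: "Brief baseline data will be collected to assess comparability of the study groups". Precision is not mentioned. On centres, Setting says: "The study will be carried out in at least five participating maternity hospitals".

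**The concern.** The plan treats centre and baseline characteristics as worth adjusting for when the outcome is binary, and contrasts this with a plain two-group comparison when the outcome is quantitative. The benefit of adjustment is most direct in the second case. In a linear model, prognostic covariates reduce the residual variance while the target, the difference in means between arms, stays the same. Logistic adjustment generally changes the odds ratio being estimated and brings no comparable narrowing of its interval.

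Birth weight plausibly depends on smoking, medical conditions and obstetric history, all of which are collected. What is at stake is some width of the confidence interval for birth weight and for any other outcome that would be compared by t-test. Validity is not at stake.

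**Working it through.** **The plan's own figure.** The only sample size stated is for the primary binary outcome: 1,604 per arm, 3,208 in total, for 5.0% against 3.0%, significance 0.05, power 0.8 (Sample size section). The two-sided two-proportion formula gives 1,506 per arm. With the continuity correction, n′ = (n/4)·[1 + √(1 + 4/(n·|p1 − p2|))]² = (1,506/4)·[1 + √(1 + 4/(1,506 × 0.02))]² ≈ 1,605, which agrees with 1,604 to within rounding. That figure is sound but does not bear on the quantitative outcomes, for which the document gives no size, power or standard deviation.

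**Inputs for the check.**
- From the document: 1,604 women per arm.
- Assumed: all women contribute the outcome; two-sided 0.05; R² (the share of outcome variance explained by centre and entry variables) of 0.05, 0.10 or 0.20. The document gives no R².

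**Step 1: the difference that the t-test detects with 80% power.**
(1.96 + 0.84) × √(2/1,604) = 0.099 standard deviations.

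**Step 2: effect of adjustment.** The residual variance is multiplied by (1 − R²). Hence:
- ratio of confidence interval widths = √(1 − R²)
- equivalent extra women = 3,208/(1 − R²) − 3,208
- power at the Step 1 difference = Φ(2.80/√(1 − R²) − 1.96)

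| Assumed R² | Width ratio | Interval narrower by | Equivalent extra women | Power |
|---|---|---|---|---|
| 0 (t-test) | 1.000 | – | – | 80% |
| 0.05 | 0.975 | 2.5% | 169 | 82% |
| 0.10 | 0.949 | 5.1% | 356 | 84% |
| 0.20 | 0.894 | 10.6% | 802 | 88% |

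**Step 3: illustration in grams.** With an assumed birth-weight standard deviation of 500 g, the detectable difference is 0.0989 × 500 = 49.5 g unadjusted. Multiplied by the width ratios, it becomes 48.2 g, 46.9 g and 44.2 g at R² of 0.05, 0.10 and 0.20.

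**The case against.** The strongest reply is that nothing here is wrong. Under randomisation a two-group t-test, or its distribution-free counterpart, is a valid comparison. The plan's main analysis of the primary outcome is itself unadjusted, with logistic regression only in support, so an unadjusted main comparison for quantitative outcomes fits its hierarchy. The article condenses a fuller protocol, and covariate models for secondary outcomes are often left to the analysis plan. The size of the gain is assumed, and at R² of 0.10 or below it is about 5% of the interval width or less.

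Most of this stands and limits the weight of the point. It does not remove it. The article is not silent on these outcomes: it names a method for them and sets it against the handling of binary outcomes, so the point concerns a stated choice and not an omitted detail.

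A reader might infer three stronger things that the document does not support:
- **That the resource argument depends on these analyses.** The Discussion ties resource implications to a reduction in preterm birth, a binary outcome, and not to mean birth weight or mean stay.
- **That unexplained centre and maternal variation is the main obstacle to seeing an effect.** Variables assumed to explain 5% to 20% of the variance leave 80% to 95% in place.
- **That length of stay would benefit most, because discharge practice differs between hospitals.** Stay may well be skewed and go to the distribution-free test that the plan allows, where the linear-model gain need not carry over.

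**Conclusion.** The point holds as a small, nearly free improvement. For birth weight, and any other quantitative outcome that would be compared by t-test, the stated analysis is valid but less precise than the data already collected allow. The interval would be about 2.5% to 10.6% narrower, and power at the t-test's 80% difference would rise to about 82% to 88%. Both ranges rest on an assumed R² of 0.05 to 0.20 and on complete outcome data for 1,604 women per arm.

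Only secondary outcomes, for which no power is stated, are affected. The primary analysis and the sample size are unchanged, and no bias or inflation of type I error is implied.

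**What to change.** In the Analyses section, where a t-test would be used, take the arm difference and its 95% confidence interval from a linear regression on arm, centre and a short list of entry variables fixed in advance, with robust standard errors. Suitable examples from the Baseline data list are age, smoking, medical conditions, and prior pregnancies including preterm birth. Report the t-test as the unadjusted check.

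Two limits should be written in:
- The covariates should not be chosen by observed imbalance, as the wording for the logistic regression now allows.
- None of the factors under Other maternal and infant explanatory factors should enter, because they arise after randomisation.

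Outcomes that go to the distribution-free test, possibly length of stay, are outside this change.

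The cost is a few lines of analysis wording and a routine model. All the variables are already collected, and no additional women or procedures are needed.
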